## Abstract

**Background:**

India contributes approximately one-quarter of the global stillbirth burden, with an estimated 460,000 stillbirths annually-one of the highest absolute burdens globally. Despite this, women experiencing stillbirth or early neonatal death face a high and largely unaddressed burden of postpartum depression, complicated grief, and functional impairment in the weeks and months following loss. No structured, community-level psychosocial support protocol is currently integrated into India's public health system, leaving Accredited Social Health Activists (ASHAs)-who routinely visit women after birth- without standardised guidance for compassionate care after perinatal loss.

**Methods:**

This protocol describes a quasi-experimental hybrid type I effectiveness-implementation study embedded within an ongoing implementation research project, SHRiSTI, aiming to reduce stillbirths in India. The Community Continuum of Care for Compassionate Support After Stillbirth (C-COMPASS) is a co-designed, community health worker–delivered counselling intervention for women experiencing stillbirth and early neonatal death. The intervention comprises five structured contacts: a telephonic follow-up within 72 h of discharge, and on Day 7, in-person visits on Day 14 and Day 21, and a Day 42 postpartum review, supported by a red-flag referral pathway. The study will use a quasi-experimental Difference-in-Differences (DiD) analytical design across four administrative blocks (two intervention, two control), with a pre-intervention observation period (approximately 10–12 weeks) and a post-intervention period (approximately 26 weeks). This design was chosen in place of a cluster-randomised controlled trial because block-level allocation is operationally determined within the existing SHRiSTI programme. The primary effectiveness outcome will be mean Edinburgh Postnatal Depression Scale (EPDS) score at 60 days postpartum, measured by independent assessors and analysed using a linear DiD model with block-level fixed effects. An expected sample of approximately 56 women per arm in the post-intervention period provides 81% power to detect a clinically meaningful difference of 3.5 EPDS points with a total anticipated enrolment of approximately 146 women. Secondary outcomes will include binary EPDS score thresholds, grief symptoms, functional disability, and incremental cost per woman counselled. Early neonatal deaths within 24 h will be included in a pre-specified sensitivity analysis. Implementation outcomes will be assessed using the Proctor et al. taxonomy.

**Discussion:**

C-COMPASS is among the first community-based interventions in India designed to address psychosocial care following stillbirth through frontline health workers. If demonstrated to be effective and feasible, this model may provide a scalable, low-cost approach for integration into India's ASHA-based maternal health system.

**Clinical Trial Registration:** The primary implementation research was registered prospectively in the Clinical Trial Registry of India (CTRI): CTRI/2024/07/069796 [Registered on: 02/07/2024].

## Introduction

1

Stillbirth, defined by the World Health Organization as foetal death at 28 or more completed weeks of gestation, remains one of the most prevalent yet under-addressed outcomes in global maternal and newborn health. An estimated 1.9 million stillbirths occur annually, with over three-quarters concentrated in sub-Saharan Africa and South Asia (1). India alone contributes approximately 460,000 stillbirths each year (2, 3), accounting for nearly one-quarter of the global burden, despite substantial progress in reducing maternal and neonatal mortality over the past decade (2, 3).

**Table 1 T1:** C-COMPASS contact schedule.

Contact	Timing	Mode	Core components
Contact 1: Early follow-up	Within 72 h of discharge	Telephone call (≥10 min)	Emotional check-in; follow-up on lactation/breast health; direct enquiry for self-harm (using scripted probe); red-flag screening
Contact 2: Check-in	Day 7 (±1 day)	Telephone call	Emotional acknowledgement and active listening; guidance on lactation suppression; assess bleeding, fever and breast pain; family engagement; provide Tele-MANAS helpline information ([name]); confirm Day 14 visit
Visit 1: Recovery	Day 14 (±2 days)	In-person home visit	First in-person visit after two telephonic counselling sessions; assess physical recovery and grief; breast health check; **Circle 1-** Heart/Feelings; **Circle 2:** Mind/Positive Thinking; family counselling; initiation of contraceptive counselling; identify and refer red flags
Visit 2: Continued recovery	Day 21 (±2 days)	In-person home visit	Assess recovery; check for physical and emotional signs of grief and breast engorgement; reinforce family support; counsel on pregnancy spacing; identify women needing further support from district psychiatrist
Contact 3: Postpartum review	Day 42 (±2 days)	Telephone call	Postpartum evaluation; follow-up on emotional wellbeing; precise contraceptive counselling; preconception planning; update ASHA registers; **Circle 3-Support** and update ASHA registers.

Beyond mortality, stillbirth is associated with profound and enduring psychosocial consequences. Women who experience stillbirth face a markedly increased risk of postpartum depressive disorder, with prevalence estimates ranging from 25% to 50% in low- and middle-income countries (4), substantially higher than among women with live births (4, 5). In addition to depression, women frequently experience complicated grief, persistent emotional distress, and functional impairment affecting social, familial, and occupational domains, with effects often extending beyond one year (6, 7). These consequences are exacerbated in contexts where perinatal loss is accompanied by stigma, blame directed at the mother, and limited access to mental health services, conditions widely documented in rural North India (8, 9).

Importantly, the psychosocial burden of stillbirth exists within a broader continuum of perinatal loss that includes early neonatal death, late miscarriage, and preterm death. Evidence suggests that grief intensity and depressive symptoms following stillbirth and early neonatal death are clinically comparable during the early postpartum period (4, 5, 7). In India, both outcomes are captured under the National Health Mission (NHM) perinatal mortality framework and together affect an estimated 700,000 families annually. Despite this substantial burden, structured psychosocial support for women following perinatal loss is not systematically integrated into India's public health system. Existing postnatal care frameworks primarily focus on women with live births, and frontline community health workers, Accredited Social Health Activists (ASHAs), receive no standardized guidance for providing care after stillbirth (10). As a result, support following perinatal loss remains informal, inconsistent, and largely undocumented. Women are often discharged within 24–48 h of delivery with minimal counselling and return to home environments where grief may be compounded by social silence, pressure, or blame. Evidence from India further highlights a critical gap in structured grief care and bereavement support at the community level, despite the established role of community health workers in delivering psychosocial and behaviour-change interventions (11–13). While several international bereavement care protocols exist, including those developed by the International Stillbirth Alliance, the American College of Obstetricians and Gynaecologists, and SANDS, these are designed for high-resource facility settings and are not readily adaptable to community-based delivery in low-resource contexts.

To address this gap, the Community Continuum of Care for Compassionate Support After Stillbirth (C-COMPASS) was co-designed by research team and other stakeholders within the SHRiSTI (Strategies to Help in Optimal Pregnancy Outcomes and Reduce Stillbirths in India) implementation research project. This care protocol aims to operationalize compassionate care into a structured, scalable, community-based response delivered through ASHAs as the primary frontline implementers. Supervisory and first-level clinical support will be provided at Health and Wellness Centres (HWCs), the most accessible level of healthcare in India, with specialist physicians available for management of complex physical and psychological complications. This study describes the protocol for evaluating C-COMPASS using an quasi-experimental effectiveness-implementation design to assess both its impact on maternal mental health outcomes and its feasibility within the existing health system.

## Methodology

2

### Study design and site

2.1

This is a prospective, quasi-experimental, Hybrid Type I effectiveness-implementation study using a Difference-in-Differences (DiD) analytical design (14). The Hybrid Type I classification-where effectiveness is the primary scientific aim and implementation outcomes are assessed concurrently-is appropriate, given that C-COMPASS has not previously been evaluated. Implementation outcomes will be assessed using the Proctor et al. (13) taxonomy rather than Reach effectiveness- adoption implementation maintenance (RE-AIM), as the latter presupposes prior effectiveness evidence (13). C-COMPASS is embedded within the SHRiSTI (Strategies to Help in Optimal Pregnancy Outcomes and Reduce Stillbirths in India) implementation research programme, which has been conducted across seven states in India since 2024. However, the C-COMPASS intervention will be implemented and evaluated only in Palwal district, Haryana, India. A cluster-randomised controlled trial is not feasible in this context because C-COMPASS is embedded within an existing programme where block-level allocation is operationally determined, ethical constraints preclude withholding an untested intervention by randomisation before evidence of effect exists, and the short enrolment window required by the SHRiSTI project's timeline cannot accommodate the lead time needed for stratified block randomisation; the DiD design provides a rigorous quasi-experimental alternative by controlling for time-invariant block-level differences through fixed effects and leveraging the natural experiment created by phased programme rollout (14).

Palwal is a predominantly rural district located approximately 80 kilometres south of New Delhi, with a total population of 1,289,685 (HMIS data). The district comprises six health blocks. The district has a sex ratio of 943 females per 1,000 males and a sex ratio at birth of 884 per 1,000 males. The female literacy rate is 68.3% among women aged 15–49 years, with 39.4% having completed 10 or more years of schooling (NFHS-5). The pregnancy rate is 116 per 1,000 women of reproductive age. The HMIS-reported stillbirth rate is 9.4 per 1,000 live births (266 stillbirths among 28,126 live births); however, this substantially underestimates the true burden. SHRiSTI's ASHA-based community surveillance documents a stillbirth rate of 17.2 per 1,000 total births. The perinatal mortality rate reported in HMIS is 14.9 per 1,000 live births which as per the SHRiSTI's ASHA-based community surveillance is around 29.2 per 1,000 live births.

The district health system comprises 1,019 ASHA workers, one District Hospital, one Sub-District Hospital, six Community Health Centres, 14 Primary Health Centres, three Urban PHCs, and 96 Health and Wellness Centres/Sub-centres (92 rural and four urban). Within SHRiSTI, a community-based stillbirth surveillance system has been established in collaboration with district health authorities, with all ASHAs actively reporting across all blocks of Palwal district.

### Study hypothesis

2.2

C-COMPASS, delivered by ASHAs to women following stillbirth, will result in significantly lower postpartum depressive symptoms at 60 days postpartum compared to routine postnatal care, and will demonstrate acceptable feasibility and implementation performance within the existing district health system**.**

### Study Aim

2.3

To evaluate the effectiveness and implementation performance of C-COMPASS, a community-based structured compassionate care protocol, among women experiencing stillbirth in Palwal district, Haryana.

#### Objectives

2.3.1

##### Primary

2.3.1.1

To assess the effect of C-COMPASS on postpartum depressive symptoms, measured by mean Edinburgh Postnatal Depression Scale (EPDS) total score at Day 60 postpartum, compared to routine care.

##### Secondary

2.3.1.2

To assess the effect on functional impairment among women with stillbirths at Day 60 postpartum.To assess the effect on grief distress among women with stillbirths at Day 60 postpartum.To estimate the proportion of women screening positive for probable depression (EPDS ≥13) in each arm, as exploratory evidence for future trial designTo explore whether effects remain consistent when early neonatal deaths (<24 h) are included alongside stillbirth.To assess the feasibility of C-COMPASS delivery within the existing ASHA system, measured by 72 h ASHA visit coverageTo estimate the incremental cost of C-COMPASS per woman counselled compared to routine care.

### Study period

2.4

The study comprises a pre-intervention observation period (March–May 2026, approximately 10–12 weeks) and a post-intervention period (May–November 2026, approximately 26 weeks), encompassing the July–October seasonal peak in stillbirths (5.2–5.6 per block per month). Data collection will be completed by December 2026.

### Study population and eligibility

2.5

*Inclusion criteria:* All women residing in the four study blocks who experience a stillbirth (intrauterine foetal death at ≥28 completed weeks of gestation) during the study period, are able to provide informed consent, and are reachable for an ASHA home visit.

*Exclusion criteria:* Women with severe cognitive impairment precluding informed consent, or those who explicitly decline participation.

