#### Identification, notification, and referral

2.6.3

Facility stillbirths will be recorded by nurses in labour room registers, case sheets, and MCP cards, and the ASHA will be notified within 24 h via SMS. For home deliveries, the ASHA will directly register the event. Following notification, the ASHA will initiate the first contact. If a home visit is not feasible, the ANM or facility nurse will assume responsibility for the initial contact.

At each contact, ASHAs will assess for predefined physical and emotional red flags using operational definitions provided in the ASHA Job Aid and covered during training. Physical red flags include heavy vaginal bleeding (soaking ≥ 2 pads per hour for two consecutive hours or clots larger than a 50-paise coin); fever (≥38 °C or feeling hot to touch with rigors); wound complications (pus, suture dehiscence, or foul-smelling discharge); breast complications with fever suggesting mastitis; and seizures. Emotional red flags include: suicidal ideation, assessed at every contact using a scripted Hindi-language probe and defined as any affirmative response or spontaneous expression of wish to die or self-harm; severe or persistent distress, defined as inability to eat or drink for >48 h, inability to sleep for >2 consecutive nights, or complete social withdrawal; and acute confusion, defined as disorientation to time, place, or person.

On identification of any red flag, the ASHA calls the CHO immediately, with an expected response within two hours. If the CHO is unreachable within 30 min and the situation is acutely life-threatening, the ASHA activates the national ambulance service (112) directly. Emotional red flags without immediate safety risk are managed through CHO-coordinated psychiatric referral within 24 h. Cases requiring specialised care will be referred to higher-level facilities, including district-level psychiatric services for complex emotional conditions.

All red-flag events, referral actions, and outcomes are documented in the C-COMPASS register column. All operational definitions, the scripted self-harm probe, the referral decision algorithm, and expected response times are addressed during the mandatory full-day ASHA training through didactic instruction and role-play scenarios, and fidelity to red-flag documentation is assessed monthly through the CHO supervision checklist.

Early neonatal deaths will be identified through the same facility-based notification pathway.

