### Block selection and matching

2.7

Four of the six SHRiSTI-surveilled blocks will be purposively selected: two allocated to the intervention arm (receiving C-COMPASS from May 2026) and two to the control arm (routine postnatal care). Block pairs will be matched based on population size, ASHA density, monthly stillbirth volume from SHRiSTI surveillance, distance to district referral facilities, and absence of any co-occurring community mental health programme.

Women in the control blocks will receive routine postnatal care as currently delivered within the National health mission program, without any C-COMPASS protocol, training, or structured referral pathway. In practice, ASHA postnatal visits in this context are designed for women with live births and focus on newborn care and breastfeeding support; no standardised protocol, training, or referral pathway exists for ASHA-delivered emotional support following stillbirth. Evidence from qualitative research conducted in the same district using a social autopsy lens found that postnatal support for bereaved women is largely informal and inconsistent, with women commonly discharged from facilities within 24–48 h with minimal counselling and returning to home environments where grief is frequently met with social silence or pressure rather than structured acknowledgement (8). No scripted emotional support, self-harm enquiry, lactation suppression guidance, or structured psychological referral pathway is routinely activated following stillbirth in the control blocks. The Tele-MANAS helpline is available as national infrastructure but is not routinely provided to bereaved women in current practice. The control condition thus represents the documented current standard of care in this setting, against which the incremental effect and cost of C-COMPASS will be estimated.

The remaining two blocks, under SHRiSTI project, will be excluded to minimise contamination, address time and resource constraints, and allow their use as potential future comparators.

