#### Implementation outcome

2.8.3

The implementation outcome will be the 72 h ASHA visit coverage rate, defined as the proportion of eligible women in intervention blocks receiving a first ASHA visit within 72 h of hospital discharge. This will be measured using ASHA registers and CHO supervision records.

This indicator is expected to be a key determinant for policy adoption. The Supplementary Table S1 details the operational definitions, and implementation outcomes assessed for this study.

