The implementation case for C-COMPASS rests on a single core argument: it is designed to be absorbed into the existing system, not added onto it. India's 1.04 million ASHAs are already mandated to conduct postnatal home visits under the Home-Based Newborn Care (HBNC) programme (10). C-COMPASS converts the visit that ASHAs already make after a stillbirth, currently an unstructured, informal, and inconsistent interaction, into a structured, documented, and evaluated care episode. The marginal resource requirement is a half-day training, a Hindi job aid, and a column in the existing ASHA register. The Tele-MANAS referral pathway ([name]) is already operational national infrastructure. The incremental cost analysis embedded in this study will quantify this argument in INR per woman counselled, the metric that government decision-makers require before considering programme adoption. The incremental cost analysis will determine whether C-COMPASS falls within the ₹200–500 per beneficiary threshold typical of scalable LMIC community health programmes. If C-COMPASS achieves the feasibility threshold of ≥70% 72 h visit coverage across both intervention blocks, it will demonstrate that ASHAs with targeted training can reliably identify and reach bereaved women in the critical early postpartum window, a finding that has direct programme planning implications at state and national level.

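### 72 h coverage is computed only over women an ASHA can reach, so women never reachable drop out of the measure used to show that ASHAs reach bereaved women

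*Protocol article*

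**What the plan says.** Section 2.5 requires residence in the four study blocks, a stillbirth at 28 completed weeks or later, ability to consent, and that women "are reachable for an ASHA home visit". The wording is the same for both arms and both periods. It sets no time limit and does not require that a visit took place.

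Section 2.8.3 defines the implementation outcome as "the proportion of eligible women in intervention blocks receiving a first ASHA visit within 72 h of hospital discharge", taken from ASHA registers and CHO supervision records. Operational definitions are referred to Supplementary Table S1, which is not shown.

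The Discussion sets a "feasibility threshold of ≥70% 72 h visit coverage across both intervention blocks" and says that, if it is met, "it will demonstrate that ASHAs with targeted training can reliably identify and reach bereaved women". Section 3.2 uses the same threshold, together with a meaningful fall in mean EPDS, as the condition for taking a scale-up plan to the state.

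These passages also bear on the point:
- Section 2.6.3, within the C-COMPASS protocol: "the ASHA will be notified within 24 h via SMS", and "If a home visit is not feasible, the ANM or facility nurse will assume responsibility for the initial contact".
- Section 2.7: control blocks continue "without any C-COMPASS protocol, training, or structured referral pathway".
- Section 2.1: surveillance runs "with all ASHAs actively reporting across all blocks of Palwal district".
- Section 2.15: research staff, not frontline workers, take consent and collect data.
- Section 3.1: some women will fall outside the notification routes; penetration data will be collected, and differences between enrolled and non-enrolled women reported.

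**The concern.** A coverage rate is meant to show how many of the women who should be reached are reached. If being reachable by an ASHA is a condition of entry to the denominator, part of the failure to reach is removed before the rate is computed. The result can then meet 70% when coverage of all identified stillbirths does not, and the Discussion's claim about identifying and reaching women would rest on a group already selected for reachability.

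A second, weaker issue follows from the same clause. Eligibility depends on ASHA practice, and ASHA practice is what C-COMPASS sets out to change in the intervention blocks from May 2026. If that altered who counts as reachable, the change would fall in the intervention/post cell. The primary model (section 2.13) removes time-invariant block differences, not a change in the mix of women in one cell.

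**Working it through.** **1. The plan's own counts.** Section 2.12 gives 4.6 stillbirths per block per month. Two blocks per arm give 9.2 per month, and 9.2 × 6 months = 55.2, close to the stated 56 per arm over 26 weeks. The full surveillance rate is used, with no deduction for unreachable women. The required number also reproduces: 2 × (1.96 + 0.842)² × 6.5² / 3.5² = 54.1, so 55 per arm, with 81.3% power at 56. Nothing below disputes these figures.

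**2. Who is counted in the 72 h rate, as written.**

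| Woman with an identified stillbirth | Denominator | Numerator |
|---|---|---|
| Reachable, visited within 72 h | yes | yes |
| Reachable, visited late or missed | yes | no |
| Classed as never reachable | no | no |

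Only the third row is lost.

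**3. Size for coverage.** Let R be the reported coverage among eligible women, u the share of identified stillbirths classed as unreachable, and c the share of those excluded women who were nevertheless contacted within 72 h. Then

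coverage of all identified = R(1 − u) + c·u.

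The documents give neither u nor c. With R = 0.70 and c = 0:

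| Assumed u | Coverage of all identified = 0.70(1 − u) | R needed for 70% of all = 0.70/(1 − u) |
|---|---|---|
| 5% | 66.5% | 73.7% |
| 10% | 63.0% | 77.8% |
| 15% | 59.5% | 82.4% |
| 20% | 56.0% | 87.5% |

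In whole numbers, with 56 identified stillbirths and about 10% unreachable, 50 women are eligible. Then 35/50 = 70% meets the threshold, while 35/56 = 62.5% does not.

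The gap shrinks if excluded women are contacted some other way. At u = 10% and c = 35%, coverage of all identified is 0.63 + 0.035 = 66.5%. At c = 70% the gap is zero.

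**4. Secondary risk to the primary estimate.** If a share s of the intervention/post cell is enrolled only because reachability changed, and those women differ by d EPDS points, the DiD estimate moves by s × d. Both inputs are assumed:
- s = 5%, d = 2: 0.1 points, 3% of the 3.5-point target.
- s = 10%, d = 4: 0.4 points, 11%.
- s = 20%, d = 6.5: 1.3 points, 37%.

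For scale, with 17 and 56 women per arm and SD 6.5, the simple DiD standard error is 6.5 × √(2/17 + 2/56) = 2.5 points.

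**The case against.** Reachable is not the same as reached. A reader might infer that every woman the ASHA fails to see within 72 h disappears from the rate. The text does not support that: section 2.5 sets no deadline and requires no completed visit, so women seen late or missed stay in as failures. This limits the distortion to women classed as never reachable.

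A reader might also infer that C-COMPASS changes reachability and so biases the primary estimate. No passage says so. The criterion is worded identically in all four cells, independent staff take consent, and section 2.6.1 says no visits are added to the existing schedule. The nurse backup applies when a home visit cannot be made, so it does not make a woman reachable for one. The 24 h SMS could matter, but section 2.6.3 does not say it is confined to intervention blocks. The mechanism is plausible but inferred, and the illustrated shifts lie well within one standard error of the estimate. It stands only as a caveat.

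Section 3.1 already promises penetration data and a comparison of enrolled with non-enrolled women. That would disclose the exclusion, but it leaves the coverage denominator unchanged. Supplementary Table S1 might define the denominator differently; if so, the main text needs to agree with it.

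Contact 1 is a telephone call in Table 1, so some women who cannot be visited at home may still be contacted early. The figures with c = 0 are therefore the largest gap for each assumed u. Finally, scale-up does not rest on coverage alone, since section 3.2 also asks for an EPDS reduction.

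**Conclusion.** The coverage point holds. As sections 2.5 and 2.8.3 are written, women classed as never reachable are left out of the rate that is set against 70% and read as showing that ASHAs reach bereaved women. A reported 70% corresponds to 66.5% down to 56% of all identified stillbirths if 5% to 20% are unreachable and none of them is contacted in time. Those shares are assumptions, and the true gap could be smaller.

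The effect on the primary DiD estimate is a secondary risk of unknown size and direction. The documents do not support stating that the estimate is biased. They do show that eligibility need not depend on the ASHA: independent staff handle consent and outcome assessment, and the sample size already treats all surveilled stillbirths as the frame.

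**What to change.** 1. In section 2.8.3, make the denominator of 72 h coverage all surveillance-identified stillbirths in the intervention blocks. The rate among reachable women may be shown as secondary.
2. In section 2.5, remove reachability by the ASHA from the inclusion criteria, so that enrolment in all four arm-by-period cells rests on residence, a surveillance-identified stillbirth, and consent taken by the independent staff.
3. Report enrolled over identified by arm and period. Section 3.1 already plans the overall proportion; the split is what would reveal a change in one cell.

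The cost is mainly wording, because surveillance already covers all blocks. Coverage will look slightly less favourable, and a few more women must be traced. Some of them will be missing at Day 60, so part of the selection moves from eligibility to missing outcomes, where it can be counted. Ascertainment would still rest on ASHA-reported surveillance; the change does not cure that.
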